### Objectives

The primary objective of this study is to assess the effectiveness of spirometry testing together with providing patients with information about their results for smoking cessation after 1 year in people older than 40 years of age with a more than 10 pack-year history who have not been diagnosed with COPD (at the outset of the study). The secondary objectives include comparing the quit rates in patients with a new diagnosis of COPD and those with normal lung function, and comparing the change in daily smoking rate between the intervention and control groups.

## Methods/Design

This is a multicentre, open-label, randomized clinical trial. Study subjects are active smokers older than 40 years of age with a more than 10 pack-year history who have not been diagnosed with COPD, from 39 general practitioner (GP) lists within the province of Gipuzkoa. The following patients will be excluded: any who are older than 80 years of age or institutionalized, as well as any who have a life expectancy of less than 1 year, have undergone spirometry testing within the previous 2 years, have been previously diagnosed with respiratory diseases (asthma, interstitial lung diseases, or COPD) that cause pattern changes in spirometry tests, or have contraindications for spirometry testing (Table 1). This clinical trial has been registered in ClinicalTrials.gov (NCT01821885).

**Table 1 T1:** Definition of the study variables

**Active smoker**	**Diagnosis of chronic obstructive pulmonary disease (COPD)**
Any patient who smokes one or more cigarettes per day will be considered an active smoker.	The criteria for the diagnosis of COPD is a post-bronchodilator FEV1/FVC ratio of < 70% (absolute value).
**Spirometry technique**	**Spirometric patterns**
**Baseline spirometry**: the nurse responsible for the spirometry testing will be experienced in the technique and familiar with the ATS/ERS criteria for acceptability (correct start with back extrapolated volume of <150 ml or 5%, curve with no marks or notches and correct end, with no leaks and lasting at least 6 seconds or with a plateau > 1 second in the volume-time curve).	Spirometry results will be considered within the normal range if FEV1/FVC > 70% (absolute value) and FVC and FEV1 > 80% of the predicted values.
	The pattern is classified as obstructive if FEV1/FVC < 70% (absolute value).
To meet the criteria for repeatability, there must be three acceptable manoeuvres and the FVC and FEV1 values in the two best two must differ by no more than 100 ml.	The pattern is classified as restrictive if FEV1/FVC > 70% (absolute value) and FVC < 80% of the predicted value.
	The pattern is classified as mixed if FEV1/FVC < 70% (absolute value) and FVC < 80% of the predicted value.
**Bronchial challenge:** After performing the baseline test, patients will be given 400 mcg of Salbutamol (in a holding chamber) and 15–20 minutes later a further spirometry test will be conducted applying the same criteria for acceptability and reproducibility as for the baseline test.	The bronchial challenge is regarded as positive when FEV1 or FVC increase by 12% or 200 ml compared to baseline values 15–20 minutes after administering 400 mcg of Salbutamol (in a holding chamber).
**Contraindications for spirometry testing**	**Quitting smoking**
• Poor general health, old age, etc.	A year after the intervention, patients will be considered to have stopped smoking if they report abstinence (defined as no of consumption of tobacco for at least 7 days) and this is confirmed by CO-oximetry (a carbon monoxide concentration in exhaled air of < 10 ppm is considered sufficient).
• Recent pneumothorax (< 6 months)	
• Unstable angina or recent acute myocardial infarction (< 6 months)	
• Recent retinal detachment (< 6 months)	
• Recent abdominal or thoracic surgery (< 6 months)	**Co-oximetry technique**
• Recent eye surgery (< 6 months)	The patient takes a deep breath and holds it for 15 seconds. They then breathe out slowly and completely (as far as they can). It is then necessary to wait for several seconds until the CO-oximeter settles and shows the exact concentration of carbon monoxide (CO) in parts per million (ppm) in the air exhaled by the patient.
• Thoracic aortic aneurysm	
• Hemoptysis of unknown origin	
• Active tuberculosis	
• Tracheostomy	
• Facial paresis	

A sample of 444 people will be recruited. The sample size calculation was based on assuming a level of significance of 5%, a quit rate after brief anti-smoking intervention only (control group) of 5% [23], an expected quit rate in the experimental group of 14% [20], and a 1:1 ratio of control to experimental subjects. Given these premises, to obtain a power of 80% to detect differences in the test of the null hypothesis Ho: p1 = p2 using a two-tailed chi-squared test for two independent samples, it would be necessary to include 166 experimental units in the reference group and a further 166 in the experimental group, making a total of 332 units for the study. Assuming a loss to follow-up of 25%, it would be necessary to recruit 222 subjects for the reference group and a further 222 for the experimental group, summing to the aforementioned total of 444 subjects for the study. The flow chart for the study is presented in Figure 1.

**Figure 1 F1:**
[figure not shown]
Study flow chart.

### Recruitment and randomization

A total of 39 doctors from a research group of an Osakidetza health region within Gipuzkoa are participating in the study. These 39 health professionals work in 22 health centers covering both rural areas (25% of the GP lists) and urban areas, with populations of over 10,000 people (75% of the GP lists).

The total catchment population of these 39 doctors is 58,540 people over 14 years of age. Primary care electronic medical records will be used to identify a sample of these patients who smoke: we will randomly select subjects from the GP lists obtaining a sample of 1775 patients (45 patients per doctor) and each doctor will be informed of the patients in his/her list selected as candidates for the study. After this, the participating doctors will check whether these patients meet the criteria for participating and contact eligible patients by phone to obtain verbal informed consent to their participation in the study and collect preliminary data. Patients will be recruited in a pre-established order from the list provided and the reasons for patient exclusion will be recorded on an individual basis. Doctors will send data on the patients recruited to the Primary Care Research Unit of the Gipuzkoa Health Region where the patients will be randomly assigned to the intervention or control group. The randomization sequence will be generated by computer and kept in the research unit. The list of patients assigned to each group will be sent to the nurses in charge of the first appointment. At this appointment, once written informed consent has been given, the interventions detailed below will be performed for each group.

### Intervention

#### *Experimental group*

The intervention consists of the nurse collecting data, performing a spirometry test and then giving the patient an appointment with their GP within 10 days. At this appointment, the doctor will deliver a brief anti-smoking intervention and provide the patient with a short explanation of the spirometry results. Both the delivery of the advice and the spirometry report will be carried out in a standardised way (in accordance with the guidelines).

#### *Control group*

The nurse will only interview the patient to collect data on the study variables and make them an appointment with their GP within 10 days. The doctor will just perform the brief anti-smoking intervention in the same standardised way as for the intervention group. These patients will not undergo spirometry during the study period of 1 year.

Nurses selected will have the skills and experience necessary for performing spirometry. After finishing this first phase of the study, two doctors with extensive experience in interpreting spirometry will assessed test results and exclude from further analysis any patients whose results do not comply with the criteria for acceptability and repeatability of the American Thoracic Society/European Respiratory Society (ATS/ERS). The nurses involved will not deliver any intervention for smoking cessation to the participants of either group; they will only conduct the interviews and carry out the spirometry, avoiding making any comments on the test results or any other issues related to the patient’s health or smoking habit.

The research doctors will receive training in the study protocol, including how to deliver the brief anti-smoking intervention and report the results of the spirometry test, and will receive a manual with written instructions, summarized in Table 2. In order to avoid variability attributable to the use of different measurement devices, the same models of spirometer (Datospir 120-C) and carbon monoxide detector (Dräger Pac 7000 CO) will be used for all the measurements.

**Table 2 T2:** Intervention by the doctor – instruction manual (summary)

**Brief anti-smoking intervention**	**Information on the spirometry results**
This will consist of a maximum 3 minutes of advice in which the health professional explains clearly to the smoker that the most effective step they could take to improve their health would be to stop smoking and provides them background information in writing. The same material will be provided to all patients and consists of two leaflets on the benefits of stopping smoking (the leaflets being those provided by the Department of Health of the Basque Government and routinely used in primary care consultations for brief anti-smoking interventions).	In the event of spirometry detecting airway obstruction (post-bronchodilator FEV1/FVC < 70%), the patient will be told that they have chronic obstructive pulmonary disease secondary to smoking and that it is very important that they stop their habit.
	In the event of spirometry values being within the normal range, the patient will be told that their respiratory function is not yet impaired and that it would be a good moment to give up smoking.
	In the event of a restrictive spirometry pattern, the patient will be told that they have impaired pulmonary function and they will be provided usual care.
	In all cases, the doctor should address any concerns or queries of the patient concerning the spirometry or any other issues that arise during the consultation.

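### Excluding patients whose spirometry fails quality review removes randomised patients from the experimental arm only and contradicts the intention-to-treat analysis

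*Protocol article*

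**What the plan says.** Recruitment and randomization: GPs send the details of recruited patients to the research unit, which randomises them. The resulting lists then go to the nurses who run the first appointment. Allocation therefore comes before any spirometry.

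Intervention, Experimental group: the nurse's part includes "performing a spirometry test and then giving the patient an appointment with their GP within 10 days". At that appointment "the doctor will deliver a brief anti-smoking intervention and provide the patient with a short explanation of the spirometry results".

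Table 2 fixes the message. With obstruction, "the patient will be told that they have chronic obstructive pulmonary disease secondary to smoking"; with normal values, "the patient will be told that their respiratory function is not yet impaired".

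Intervention, Control group: controls have an interview and the brief advice, and no spirometry during the study year. The next paragraph sets the quality review: "After finishing this first phase of the study, two doctors with extensive experience in interpreting spirometry will assessed test results", and they will "exclude from further analysis any patients whose results do not comply with the criteria for acceptability and repeatability". No other consequence of failing the review is stated.

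Table 1 describes an earlier quality step: "the nurse responsible for the spirometry testing will be experienced in the technique and familiar with the ATS/ERS criteria for acceptability". The repeatability criterion is: "there must be three acceptable manoeuvres and the FVC and FEV1 values in the two best two must differ by no more than 100 ml".

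Statistical analysis: the data are to be analysed by intention to treat.

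**The concern.** Two problems arise from the same sentence.

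1. **Exclusion after randomisation in one arm.** Only patients who had the test can fail its review. A control who would have produced an unacceptable test stays in the analysis; the matching experimental patient leaves it. The arms are then no longer the groups that randomisation formed. Whether a patient can complete three acceptable, repeatable manoeuvres may depend on cooperation, symptoms or lung function, and any of these may be related to quitting. The comparison of quit rates is then open to selection bias, and the rule cannot stand beside an intention-to-treat analysis.

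2. **Disclosure is not tied to the review.** The information about the test is part of what the trial is testing. On the natural reading, the GP gives it within 10 days of the test, while the review follows a phase of the whole study. The stated consequence acts on the analysis and not on what the patient was told. A patient may therefore hear a result that the trial later rejects.

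**Working it through.** **Inputs.** From the sample size paragraph in Methods/Design: quit rates 5% (control) and 14% (experimental), two-sided 5% test, 80% power, 1:1 allocation, 25% loss to follow-up. The rejection rate f is not in the document; 5%, 10% and 20% are assumptions.

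**The plan's own figure.** With pooled variance and mean rate 0.095:

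n = [1.96 × √(2 × 0.095 × 0.905) + 0.8416 × √(0.05 × 0.95 + 0.14 × 0.86)]² / 0.09² = 165.4, so 166 per group.

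166 / 0.75 = 221.3, so 222 per group and 444 in total. The stated size is reproduced, and power at 166 per group is 80.1%. The 25% allowance is for loss to follow-up; rejected tests would come on top of it.

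**Sequence.** Randomisation, then the nurse visit (test in the experimental arm only), then the GP visit within 10 days (result disclosed), then the expert review after the study's first phase, then exclusion. The review can remove experimental patients only.

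**Power under the plan's own exclusion.** Control stays at n₁ = 166, the experimental arm becomes n₂ = 166 × (1 − f), and quit rates are unchanged.

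Power = Φ[(0.09 − 1.96 × SE₀) / SE₁], with SE₀ = √(p̄(1 − p̄)(1/n₁ + 1/n₂)) and SE₁ = √(0.05 × 0.95/n₁ + 0.14 × 0.86/n₂).

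Example, f = 10%: n₂ = 149.4; p̄ = (8.3 + 20.916)/315.4 = 0.0926; SE₀ = 0.0327; SE₁ = 0.0330; power = Φ(0.784) = 78.4%.

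**Size of a possible selection bias.** If the whole experimental arm quits at rate p and the rejected patients at rate q, the rate left after exclusion is (p − f × q)/(1 − f). The values of q are illustrations: nobody quits (q = 0), or they quit at twice the arm's rate (q = 28% when p = 14%; q = 10% when p = 5%).

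| Assumed f | Rejected of 222 | n₂ | Power | p = 14%: rate left, q = 0 | p = 14%: rate left, q = 28% | p = 5% (no effect): rate left, q = 0 | p = 5%: rate left, q = 10% |
|---|---|---|---|---|---|---|---|
| 5% | 11 | 157.7 | 79.3% | 14.7% | 13.3% | 5.3% | 4.7% |
| 10% | 22 | 149.4 | 78.4% | 15.6% | 12.4% | 5.6% | 4.4% |
| 20% | 44 | 132.8 | 76.3% | 17.5% | 10.5% | 6.25% | 3.75% |

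Example: (0.14 − 0.10 × 0)/0.90 = 15.6%.

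The loss of power is small. The shift in the experimental rate can go either way, and it remains when there is no true effect, because the control rate is not filtered in the same way.

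**The case against.** **Further analysis may mean only the analyses that use spirometry.** The sentence does not name the analysis, and the authors may have meant only the COPD-versus-normal comparison. But it speaks of excluding patients, without limit. If the narrow meaning is intended, the text has to say so, and the fix below does that.

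**Both arms may be tested.** The Abstract says that all patients have spirometry, which contradicts the Control group section. If the Abstract were right, exclusions could fall on both arms. They would still contradict intention to treat, and still only intervention patients would be told a result.

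**Late review is a defensible pragmatic choice.** A test done by a nurse and reported by a GP is the service that primary care would use. Expert reading before every GP visit would be a more resource-intensive service. This stands, and it is why earlier review is only optional. It also argues for keeping patients with imperfect tests in the analysis.

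**First phase is undefined, and Table 2 only summarises a manual that is not shown.** Both are true. But the wording refers to a phase of the study. Even if that means only the nurse visits, patients tested early would see their GP before it ended, unless all testing across 22 centres finished within about 10 days. The manual may say how GPs handle a poor test; it does not undo an exclusion rule that the article states.

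**Stronger readings that the document does not support.** A reader might infer that some patients certainly will be given a wrong result. No rejection rate is given, the nurse applies the criteria at the time of testing, and a test can miss the 100 ml margin and still be classified correctly. A reader might also infer that rejected tests dilute the experimental quit rate and cost much power. That assumes that such information has no effect, overlooks that the plan drops these patients, and would not be cured by reviewing tests sooner. Nor does the lateness of the review cause the one-arm exclusion: the same rule applied earlier would still act after randomisation.

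**Conclusion.** The exclusion rule is wrong as written. It removes randomised patients from the experimental arm only, on a feature that may be related to quitting, and it contradicts the stated intention-to-treat analysis. This rests on the Control group section being right that controls have no spirometry.

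The size cannot be fixed from the document. With assumed rejection of 5%, 10% or 20% and unchanged quit rates, power is about 79%, 78% or 76% against a planned 80%. The larger risk is selection bias of unknown direction; in the illustrations above it moves a 14% experimental rate to between 10.5% and 17.5% at 20% rejection.

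The disclosure point is secondary. The sections do not say whether disclosure depends on the expert review, so some patients may be told a result that is later rejected. Their number is unknown and is reduced by the nurse's check at testing.

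**What to change.** 1. In the Control group section, delete the exclusion as it applies to the between-group comparison. State that every randomised patient stays in the intention-to-treat analysis whatever the outcome of the quality review.
2. Have the two doctors record each test as acceptable or not, as a study variable. Use it only in a sensitivity analysis labelled as such and in the secondary comparison of new COPD with normal function.
3. Reconcile the Experimental group section, the Control group section and Table 2 on whether disclosure depends on the expert review, and define the first phase. What is said to a patient whose test is not acceptable is for the clinical team to settle. Correct the Abstract or the Control group section on whether controls are tested.
4. Optional: where turnaround allows, the same two doctors read tests on a rolling basis before the GP visit.

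Items 1 to 3 cost a few sentences and one recorded variable, with no added patients or tests. Item 4 costs a faster review, because 10 days is the longest interval allowed and some visits will come sooner.

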**Methods/Design:**

This is to be a randomized, multicentre, open-label clinical trial. A total of 444 smokers over 40 years of age will be recruited by 39 general practitioners from 22 health centers. Primary objective of this study is to assess the effectiveness of spirometry together with information regarding the test for smoking cessation after 1 year in smokers over 40 years of age with a more than 10 pack-year history and no previous diagnosis of chronic obstructive pulmonary disease. Groups of 45 patients who smoke will be randomly selected from the lists of the participating doctors. The names will be sent to the corresponding doctors who will contact candidate patients and assess whether they meet the selection criteria. Patients who meet these criteria will be randomly allocated to an intervention or control group. For patients in both groups, a nurse will conduct an interview and perform a spirometry test to measure forced vital capacity. Then, all patients will be referred for an appointment with their doctor for brief anti-smoking intervention, patients from the intervention group additionally being informed about the result of the spirometry test. After 1 year, smoking status will be assessed and, in those who report that they have quit smoking, abstinence will be confirmed by co-oximetry. Data will be analyzed on an intention-to-treat basis using the chi-squared test for outcomes and binary logistic regression if it is considered to be necessary to adjust for confounding variables.

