### Statistical analysis

Data will be analyzed on an intention-to-treat basis using SPSS 19.0 software. Given that the primary outcome measure is categorical in nature (whether patients do or do not quit smoking), the final comparison will be performed using chi-squared tests and effect size estimates will be expressed as relative risk (RR), absolute risk reduction (ARR), and number needed to treat (NNT) with the corresponding 95% confidence interval (95% CI). Continuous variables will be assessed with the Student’s t-test, if the data meet the assumption of normality, and otherwise with the corresponding non-parametric test.

If this initial analysis demonstrates the need for multivariate analysis, binary logistic regression analysis will be used. This type of model will allow us to compare the primary outcome measure between groups adjusting for any observed differences, and thus minimizing the potential for confounding bias in the final comparison between intervention and control groups. In this case, all the estimations would be expressed as odds ratios with 95% confidence intervals.

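### Dropping randomised patients for poor-quality spirometry contradicts the stated intention-to-treat analysis and leaves the primary comparison open to bias of unknown size and direction

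*Protocol article*

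**What the plan says.** Allocation comes before testing. In Recruitment and randomization, the research unit randomises the recruited patients, and then "The list of patients assigned to each group will be sent to the nurses in charge of the first appointment".

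In the Methods, spirometry belongs to one arm. The experimental arm is described thus: "The intervention consists of the nurse collecting data, performing a spirometry test and then giving the patient an appointment with their GP within 10 days". Of the controls, the article says: "These patients will not undergo spirometry during the study period of 1 year".

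The exclusion rule stands in the text under Control group. It begins "After finishing this first phase of the study, two doctors with extensive experience in interpreting spirometry" and goes on to say what these reviewers do: "exclude from further analysis any patients whose results do not comply with the criteria for acceptability and repeatability". The criteria meant are the ATS/ERS ones. Table 1 gives the repeatability requirement: "there must be three acceptable manoeuvres and the FVC and FEV1 values in the two best two must differ by no more than 100 ml". It applies the same criteria to the post-bronchodilator test.

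Statistical analysis then states: "Data will be analyzed on an intention-to-treat basis using SPSS 19.0 software".

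The Abstract differs from the Methods on who is tested: "For patients in both groups, a nurse will conduct an interview and perform a spirometry test to measure forced vital capacity".

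**The concern.** The rule removes people, not just test values, and it acts on something observed after allocation. Under the Methods, a control patient can never meet the condition for removal, so one arm is filtered and the other is left whole. An analysis set built in this way is not intention-to-treat, whatever it is called.

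The primary result is at stake. Whether a smoker can or will produce three acceptable manoeuvres may be related to health, cooperation or motivation, and any of these may be related to quitting. If so, the filtered arm no longer corresponds to the unfiltered one, and the planned relative risk, absolute risk reduction and number needed to treat no longer describe the randomised comparison. Logistic regression on observed differences, which the plan holds in reserve, cannot be relied on to restore it. Events are also few: at the assumed 5% quit rate, 166 controls yield about 8 quitters (166 × 0.05 = 8.3), so selective removal from one arm can move the estimate.

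The question asked changes too. The objective concerns spirometry together with information about the result. In practice that strategy includes patients whose test turns out unusable.

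**Working it through.** **1. The plan's own figure.** Inputs from the sample-size paragraph in Methods/Design: control quit rate 5%, experimental 14%, two-sided 5% level, 80% power, 1:1 allocation, 25% loss to follow-up. With pooled variance and no continuity correction, and mean rate (0.05 + 0.14)/2 = 0.095:

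n = [1.960 × √(2 × 0.095 × 0.905) + 0.842 × √(0.05 × 0.95 + 0.14 × 0.86)]² / 0.09² = 165.4, so 166 per arm.

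166 / 0.75 = 221.3, so 222 per arm and 444 in total. Both stated figures reproduce. Power at 166 per arm is 80.1%.

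**2. Bias when there is no true effect.** Let f be the fraction of the experimental arm excluded and r the quit rate of the excluded divided by that of the retained. If the whole arm quits at 5%, then 0.05 = q(1 − f) + r·q·f, where q is the retained rate. Hence

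q = 0.05 / (1 − f + f·r), and apparent RR = q / 0.05 = 1 / (1 − f + f·r).

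The documents give neither f nor r. I assume f = 10% or 20% (22 or 44 of 222, leaving 200 or 178) and let r run in both directions. Type I error is the exact binomial rejection probability of the uncorrected two-sided chi-squared test, with 222 controls at 5% against 200 or 178 retained patients at rate q, and no other loss.

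| Quit rate of excluded relative to retained (r) | RR, f = 10% | RR, f = 20% | Type I error, f = 10% | Type I error, f = 20% |
|---|---|---|---|---|
| 0 (never quit) | 1/0.90 = 1.11 | 1/0.80 = 1.25 | 5.6% | 8.7% |
| 0.5 | 1/0.95 = 1.05 | 1/0.90 = 1.11 | 5.0% | 5.8% |
| 1 (unrelated) | 1.00 | 1.00 | 4.8% | 4.9% |
| 2 | 1/1.10 = 0.91 | 1/1.20 = 0.83 | 5.4% | 6.4% |

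With no exclusion (222 against 222) the exact type I error is 4.8%.

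**3. Precision.** The only attrition allowed for is the 25% loss to follow-up. If that loss occurs in full, does not overlap with the quality exclusions, and exclusion is unrelated to quitting, the experimental arm falls from 166 to 149 (f = 10%) or 133 (f = 20%). Power for 5% against 14% falls from 80.1% to 78.3% or 76.3%.

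**4. With the fix.** Keeping every randomised patient in the allocated arm leaves 166 evaluable and 222 recruited per arm. The sample size needs no change.

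**The case against.** *The rule may concern only the spirometric analyses.* It sits in a paragraph on test quality and could have been meant for the comparison of new COPD with normal lung function, leaving the statistical section to govern the primary comparison. That is possible. But the text removes patients rather than test values, and nothing in the article limits the rule to a secondary analysis. If the narrow meaning was intended, the fix simply states it.

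*The one-sidedness is not beyond dispute.* The Abstract has both groups tested. The Methods are more specific and say the opposite for controls, so I read them as operative, but the article does contradict itself on the fact that makes the exclusion one-sided. If both arms were tested, the filter would apply to both. It would still act after randomisation and still depart from intention-to-treat.

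*A reader might infer that the bias favours the intervention*, because patients who cannot complete the test could be less motivated to quit. The documents do not support this. Nothing in them links test quality to quitting, and the opposite can be argued: the Discussion cites observational studies with higher quit rates after a COPD diagnosis, and if impaired patients failed the manoeuvres more often (an assumption), the exclusion would work against the intervention. If failure is unrelated to quitting, there is no bias, only some lost precision.

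*A reader might also infer that patients are removed after hearing their result and advice.* The article says only that the review follows the first phase, which it does not define. Exclusion after randomisation is all that is certain.

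*The effect may be small.* Experienced nurses may keep failures few, and outside the extreme case of 20% excluded with none ever quitting, type I error in the table stays at or below 6.4%. This stands as a limit on size. It does not remove the contradiction.

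**Conclusion.** The point holds as an internal contradiction affecting the primary analysis. The exclusion rule and the intention-to-treat statement cannot both be followed, and under the Methods the rule removes patients from the intervention arm alone. That much rests on the text and needs no assumption.

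The consequence for the estimate is less certain. The comparison is open to bias, but the documents fix neither its size nor its sign. Over the assumed range (10–20% excluded, excluded patients quitting at anything from zero to twice the rate of the others, no true effect) the apparent relative risk runs from 0.83 to 1.25. The power loss of about two to four percentage points is secondary and depends on the conditions in step 3 of the working.

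The point should be settled before analysis, because it decides who enters the primary comparison and the correction is needed on either account of who is tested.

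**What to change.** Replace the exclusion rule with wording such as:

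> All randomised patients are analysed for smoking cessation in the group to which they were allocated, whatever the quality of their spirometry. Patients with non-acceptable tests are excluded only from analyses that need a valid spirometric classification (COPD versus normal lung function).

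An analysis without these patients may be shown as a sensitivity analysis, labelled as a non-randomised comparison. The Abstract and the Methods should also be reconciled on whether controls have spirometry.

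The cost is a change of wording, plus keeping these patients in the one-year follow-up already planned for everyone: the telephone call and, for those who say they have quit, the visit for exhaled-CO confirmation.
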